Existing data from trials involving non-pregnant patients are not informative due to differences in age, stage of HBV, frequency of HBV DNA testing and immune response and pharmacokinetics of TDF in pregnant women compared with non-pregnant patients.^17–20^ Pharmacokinetic studies have established that the area under the curve and maximum drug concentration (C_max_) of TDF are decreased in the second and third trimester of pregnancy, and clearance is increased.^18 21–24^ In a systematic review of TDF pharmacokinetics in pregnancy, none of the manuscripts reported reaching the TDF C_max_ of 300 ng/mL the efficacy threshold determined in non-pregnant HBV infected women.^23^ These data suggest that TDF dosage and treatment initiation that are accurate for HIV and non-pregnant HBV-infected patients may not be accurate for pregnant HBV-infected women.

While some of the safety issues have been resolved with the use of TDF for prevention of MTCT of HIV, gaps remain regarding HBV.^25 26^ The main barriers to implementation of TDF are a (1) lack of knowledge by the women of hepatitis B, of their infection status, and of prevention strategies,^27^ (2) poor adherence to the prophylactic drug regimen,^9^ and (3) potential for hepatitis flares after postpartum drug discontinuation.^28^ All of these need to be evaluated and addressed in limited-resource settings where HBV is highly endemic.^29^

The aim of this prospective interventional study is to determine the appropriate time in pregnancy to initiate TDF treatment of HBV in order to reach HBV DNA <100 IU/mL at delivery. Knowing this will allow future studies where TDF can be initiated at the appropriate time so that HBIG may not be needed to prevent MTCT of HBV. The viral kinetics of HBV DNA in pregnant women receiving daily oral TDF commenced before 20 weeks gestation will be measured monthly. Infants will receive HBIG and birth-dose monovalent HBV vaccine. MTCT will be assessed at 2 months post partum. While the study population is pregnant women attending antenatal and birth services on the Myanmar–Thailand border, the study has worldwide application to women who are pregnant and HBV positive. Moreover, we will study safety, feasibility and potential barriers to implementation of TDF in routine ANC in a limited-resource setting.

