### Objectives

The primary objective is to estimate the time to HBV DNA suppression <2 log10 IU/mL (or <100 IU/mL) in HBV DNA positive women who start TDF late in the first or early in the second trimester.

Secondary objectives include: estimation of the proportion of women with HBV DNA <2 log10 IU/mL (or <100 IU/mL) at delivery; the concentration of TDF in maternal and cord blood at birth in women who have detectable HBV DNA and a subset of women with undetectable HBV DNA; to monitor the safety of TDF on the Myanmar–Thailand border in pregnant women with low health literacy rates^30^ and address potential barriers to implementing TDF in early pregnancy to prevent MTCT of HBV; to determine the rate of hepatic flares post partum after cessation of TDF; to estimate the proportion of cases of vertical transmission in infants of 2 months of age; to assess fetal growth by monthly ultrasound, and infant growth at 1, 2, 4 and 6 months and neurodevelopment at 6 months.

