### Study recruitment and enrolment

Pregnant women aged 16–49 years with a singleton viable pregnancy, an HBV infection, and an estimated gestational age of 12 to <20 weeks determined by ultrasound will be counselled about the disease and invited to participate in the study. Part of this information session will include counselling on HBV in general, the need for adherence to the study drug and benefits and risks of the treatment. If a woman is interested, a blood sample will be collected to determine if she meets the criteria for enrolment, that is, HBeAg positive or HBV DNA >1.9 log 10 (>85 IU/mL). Women will be informed of the results at the next visit and be enrolled and started on TDF if all inclusion criteria are met (table 1).

**Table 1 T1:** Inclusion and exclusion criteria

Inclusion criteria	Exclusion criteria
Willing and able to give informed consent for participation in the study	Negative qualitative HBV DNA if HBeAg negative
Hepatitis B infected (HBsAg confirmed positive and qualitative HBV DNA positive in HBeAg-negative mothers)	HIV positive or on immunosuppressive therapy for other illnesses
Female, 16–49 years	Elevated creatinine (>1 mg/dL)
EGA 12–20 weeks at start TDF	Abnormal serum phosphate (<2.4 and >4.5 mg/dL)
Willing to take TDF daily during pregnancy	History of kidney disease
Plans to deliver at SMRU	History of pregnancy complications

EGA, estimated gestational age; HBeAg, hepatitis B e antigen; HBsAg, hepatitis B surface antigen; SMRU, Shoklo Malaria Research Unit; TDF, tenofovir disoproxil fumarate.

SMRU has conducted research for over two decades and the trust in antenatal services is high resulting in high follow-up rates in ANC as well as in previous studies.^36^ If a woman misses an appointment, she will be contacted using her phone number if applicable or the healthcare workers will reach out to her community or family to find her.

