#### Laboratory tests

A maternal whole blood sample obtained by venipuncture will be collected at study entry, monthly until delivery, at birth and at two postpartum visits (figure 2). Maternal HBV DNA, alanine aminotransferase (ALT) and creatinine will be measured at all scheduled visits for the mother. Serum phosphate will be measured at baseline and at birth.

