### Data analyses

#### HBV viral kinetics

The Kaplan-Meier method will be used to estimate the median time from initiation of TDF to an HBV DNA <100 IU/mL including all women and then, based on the distribution of HBV DNA, stratified by high versus low HBV DNA groups. We expect those with low HBV DNA at enrolment to have <100 IU/mL at the time of delivery, but it is important to include them in this study to calculate the trajectory of decline and determine how long they need to be treated to reach HBV DNA <100 IU/mL. A generalised estimating equation model will be used to assess whether baseline HBV DNA and adherence to TDF are associated with the logarithmically transformed HBV DNA over time. A proportional hazard model will be constructed to assess the HR of reaching undetectable HBV DNA adjusting for the baseline HBV DNA concentration and adherence to TDF (# pills actually taken/# pills that should have been taken). For missing HBV DNA data, depending on the reasons for being missing, imputations using multiple imputations by chained equations will be used. Sensitivity analyses will then be performed comparing analyses using complete and imputed data sets. The proportion of women with undetectable HBV DNA at delivery will be reported with 95% CI in all women and by high versus low HBV DNA groups. Median and IQR of HBV DNA at baseline and each visit will be reported. Then, HBV DNA will be logarithmically transformed and the median HBV DNA at baseline and at delivery will be compared using paired t-tests. Additional analyses may be conducted to further explore the data.

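### HBV DNA is sampled about monthly, so the primary time to suppression is interval-censored; the ordinary Kaplan-Meier median named for it comes out about two weeks late

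*Protocol article*

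**What the plan says.** Under Objectives: "The primary objective is to estimate the time to HBV DNA suppression <2 log10 IU/mL (or <100 IU/mL"). The women concerned begin TDF around the end of the first trimester or the start of the second. The target is therefore the time at which the threshold is crossed.

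The sampling is set in three places:
- The background section says: "The viral kinetics of HBV DNA in pregnant women receiving daily oral TDF commenced before 20 weeks gestation will be measured monthly".
- Under Laboratory tests, maternal blood is "collected at study entry, monthly until delivery, at birth and at two postpartum visits".
- Table 2 marks HBV DNA at the start, at the monthly visits, at delivery and at 1 month post partum.

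The analysis is set under HBV viral kinetics: "The Kaplan-Meier method will be used to estimate the median time from initiation of TDF". The event is HBV DNA below 100 IU/mL, and the analysis covers the whole cohort first and the high and low HBV DNA groups after that. The same paragraph says that women with low HBV DNA are included partly to learn how long they must be treated to get below the threshold. It adds: "A proportional hazard model will be constructed to assess the HR of reaching undetectable HBV DNA". That model adjusts for baseline HBV DNA and adherence. The paragraph promises a 95% confidence interval for the proportion undetectable at delivery and states none for the median time.

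The article gives no rule for dating suppression between visits and names no interval-censored method.

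**The concern.** A woman who is at or above 100 IU/mL at one visit and below it at the next crossed at some unknown moment in between. Ordinary Kaplan-Meier cannot use that interval. It needs one time, and the time at hand is the visit at which suppression is first seen, which is the right-hand end of the interval. Every event is then dated late or, at best, on time. The errors share one direction, so they do not average out and a larger sample does not remove them.

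At stake is the main deliverable. The study exists to say when in pregnancy TDF must start for HBV DNA to be below the threshold by delivery, and the median time to suppression is the figure from which that is read. Two weeks is a quarter of the eight-week enrolment window (12 to <20 weeks: 2/8 = 25%). It is also nearly a quarter of the mean 8.6 weeks of pre-delivery TDF that the introduction reports from a cited third-trimester trial (2/8.6 = 23%).

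The low HBV DNA group is the most exposed, because many of these women may be suppressed before their first monthly sample.

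**Working it through.** **1. The plan's own figure.** The Sample size section gives n = 1.96² × p(1 − p)/d². With p = 0.5 and d = 0.08 this is 3.8416 × 0.25/0.0064 = 150.06, so the stated 150 (enrolling 170) reproduces. It sizes the proportion undetectable at delivery. It does not concern the median time and is unaffected by this point.

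**2. Inputs.**
- From the article: monthly HBV DNA plus delivery and post partum; start at "an estimated gestational age of 12 to <20 weeks determined by ultrasound"; n = 150.
- Assumed, because the article does not give them: a month taken as 4 weeks; visits on schedule or moved by up to ±0.5 or ±1 week; delivery near 39 weeks, hence about 39 − 20 = 19 to 39 − 12 = 27 weeks on TDF before birth; Weibull times with shape 1.0 or 1.5; true medians from 6 to 14 weeks.

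**3. Expected size by hand.** If the crossing is roughly uniform between visits, the mean delay until it is seen is half the interval: 4/2 = 2 weeks. With a calendar month of 4.35 weeks it is about 2.2 weeks.

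**4. Simulation (200 runs per scenario).** Kaplan-Meier median, dated at the first suppressed visit:

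| True median (weeks) | Mean Kaplan-Meier median (weeks) | Late by (weeks) |
|---|---|---|
| 6 | 8.0–8.3 | 2.0–2.3 |
| 8 | 10.0–10.5 | 2.0–2.5 |
| 10 | 12.1–12.2 | 2.1–2.2 |
| 12 | 13.7–14.4 | 1.7–2.4 |
| 14 | 16.0–16.3 | 2.0–2.3 |

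Across all scenarios, including true medians of 9 and 11 weeks, the error was +1.3 to +2.7 weeks. Kaplan-Meier applied to the true crossing times was off by at most 0.4 weeks, so the dating causes the error, not the estimator or the sample size.

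**5. Coverage.** A nominal 95% log-log interval for the Kaplan-Meier median covered the true median in 0% to 87% of runs in nearly all scenarios (for example 0–14% at a true median of 6 weeks, 53–80% at 14 weeks). It reached 97–98% only where the true median fell exactly on a fixed visit, at 8 or 12 weeks with no shift in visit dates.

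**6. Low HBV DNA group.** If more than half of the group suppress before the first monthly visit, the visit-dated curve first drops at that visit and passes 50% there. The reported median is then about 4 weeks, whether the true median is 1, 2 or 3 weeks.

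**7. Interval-censored estimates on the same data.** An interval-censored Weibull fit had bias of −0.07 to +0.22 weeks and coverage of 92–99%. The Turnbull estimate with interpolation had bias of about −0.3 to +0.4 weeks (60 runs per scenario).

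**8. Hazard ratio, checked separately (300 runs each).** With visit-dated events, a true 0.50 gave 0.495 with Efron ties and 0.541 with Breslow ties. A true 0.30 gave 0.298 (Efron, coverage 96%) and 0.338 (Breslow, coverage 89%).

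**The case against.** The strongest reply is that the article nowhere says suppression is dated at the first suppressed visit. That is a default reading, and an analysis plan that is not shown could set another rule. The error has a known direction and modest size, and the HBV DNA values are kept, so re-analysis is always possible. The same section also plans a generalised estimating equation for log HBV DNA and summaries by visit, neither of which dates an event, and the proportion undetectable at delivery is untouched. Finally, if the target were the time to first documented suppression, the Kaplan-Meier median would be valid for this visit schedule.

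Most of this is fair and limits the point without removing it. The article itself names the primary estimator, and that estimator does not suit the sampling. The objective is worded as time to suppression, not time to its documentation. The other planned analyses do not yield the primary median.

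It is also fair that the interval-censored Weibull fit was tested on Weibull data, which flatters it. Turnbull, which assumes no shape, is the fairer comparison and still does much better than visit-dated Kaplan-Meier.

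Three stronger readings are tempting and are not supported:
- **That a stated 95% confidence interval is wrong.** The article promises one for the proportion at delivery only, so the coverage figures concern any standard interval that might be attached to the median.
- **That the proportional hazards model is biased late and must be replaced.** A hazard ratio is not a date. It is nearly unbiased with Efron ties and is pulled towards 1 only with Breslow ties, and the article names no tie method.
- **That the adherence covariate conditions on the future.** The article defines the pill ratio but not its time window. Pills are counted at every monthly visit, so a ratio up to each visit can be computed. Harm would also need adherence to change after suppression, which nothing in the article suggests.

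**Conclusion.** The point holds for the primary median. With about monthly sampling, time to HBV DNA below 100 IU/mL is interval-censored, and the named Kaplan-Meier method, with events dated in the default way, overstates the median by roughly half a visit interval: about 2 weeks, with a range of 1.3 to 2.7 weeks. A standard confidence interval around that median would usually under-cover the true time. In the low HBV DNA group the estimate may reflect little more than the date of the first visit.

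The direction and the half-interval size follow from the visit schedule. The exact range and the coverage figures rest on the assumptions of 4-week visits, Weibull times, delivery near 39 weeks and true medians of 6 to 14 weeks. The point does not extend to the sample size, the proportion undetectable at delivery or the choice of a proportional hazards model.

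**What to change.** For each woman, record the last visit at or above 100 IU/mL and the first visit below it, and use these as the bounds of the event time (right-censored if suppression is never seen). Estimate the primary curve and median with the Turnbull nonparametric estimator plus an interval-censored parametric model, overall and by high and low HBV DNA group. Report ordinary Kaplan-Meier as a sensitivity analysis. For the hazard ratio, specifying Efron ties or a discrete-time model is enough.

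At minimum, if Kaplan-Meier stays primary, label its result as time to first documented suppression under monthly sampling, and say so wherever the median is used to discuss start time.

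The cost is a few lines of analysis text and standard software, with no extra visits, samples or participants. The downsides are less familiar output and a Turnbull curve that is undetermined within intervals, which is why the parametric model is reported beside it.

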## Introduction

### Background and rationale

In 2016, it was estimated that only 1 in 10 of the 257 million people living with hepatitis B virus (HBV) were aware of their infection and of those, 1 in 7 were on treatment, which is less than 2% of the HBV infections globally.^1^ The current sustainable development goals aim to reduce the prevalence of HBV by 90% by 2030.^2^ An essential route to reach this goal is prevention of mother-to-child transmission (MTCT) of HBV, the most common source of infection. Pregnancy provides a window of opportunity in the life of an adult to advocate for a screening intervention, raising awareness of HBV infection, potentially resulting in positive impacts on prevalence. Unfortunately, both screening and prevention efforts are impeded by lack of access to universal healthcare and essential health services, a problem relevant to half of the world’s population.^3^

Maternal HBV infection is an important communicable disease on the Myanmar–Thailand border^4^ and in other parts of Asia, the western Pacific and African Region, where more than 6% of adults are infected.^1^ In antenatal clinics at the Shoklo Malaria Research Unit (SMRU) clinics, the hepatitis B surface antigen (HBsAg) prevalence is 6.4%–8.3% with a hepatitis B e antigen (HBeAg) prevalence of 32.7% in those positive for HBsAg.^4 5^ Mothers who are HBeAg positive are at the highest risk of transmitting HBV to their infants, which is the basis for specifically targeting this group for neonatal hepatitis B immunoglobulins (HBIG) within 72 hours of life. In infants born to HBeAg-positive mothers and provided HBIG and HBV vaccine, prevention of MTCT fails in an estimated 8%–32% of cases.^6^ Overall, there are two reasons to find alternatives to HBIG: (1) failure to prevent MTCT in infants born in HBeAg-positive women, and (2) for the 50% of the world’s population without universal healthcare who lack access to HBIG as it remains a specialised product that is costly, requires a cold chain and has a restrictive prescription window to be effective.^7^

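### The step from time-to-suppression to a recommended start of TDF assumes decline does not depend on gestation at start, and no named kinetics analysis checks this within the enrolled window

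*Protocol article*

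**What the plan says.** The Background and rationale section of the protocol article gives the aim as to "determine the appropriate time in pregnancy to initiate TDF treatment of HBV in order to reach HBV DNA <100 IU/mL at delivery". The Objectives section makes this operational: the primary objective is the time to HBV DNA below 100 IU/mL in women who start TDF late in the first or early in the second trimester.

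The recruitment text takes women at "an estimated gestational age of 12 to <20 weeks determined by ultrasound"; Table 1 has "EGA 12–20 weeks at start TDF". The two differ only at the 20-week boundary, which does not affect this point. A woman qualifies if she is "HBeAg positive or HBV DNA >1.9 log 10 (>85 IU/mL").

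The section on HBV viral kinetics plans:
- Kaplan-Meier from TDF initiation, overall and by high versus low HBV DNA;
- a GEE with baseline HBV DNA and adherence as predictors;
- a proportional hazard model "adjusting for the baseline HBV DNA concentration and adherence to TDF";
- the proportion undetectable at delivery, overall and by high versus low HBV DNA.

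Gestational age at TDF start and HBeAg status appear in none of these. Timing is used elsewhere: the time of TDF initiation is compared by transmission status (Secondary analyses), and treatment duration enters the flare models (Hepatic flare).

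**The concern.** A Kaplan-Meier curve that starts at TDF initiation yields a duration. The aim asks for a point in pregnancy. The link between them is to subtract the duration from the expected date of delivery, and this is valid only if a woman who starts at one gestation suppresses as fast as a woman who starts at another.

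The article itself treats pregnancy as altering drug exposure: the area under the curve and maximum concentration of "TDF are decreased in the second and third trimester of pregnancy, and clearance is increased". That makes it reasonable to ask whether decline varies with gestation at start. Start gestation is known for every woman at entry, yet no named kinetics analysis uses it. If time to suppression did vary across the window, the pooled median would average over the variation and the reader would not see it.

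A smaller, separate matter is HBeAg. It is one of the two entry routes and decides whether the infant receives HBIG, and the study is meant to inform later studies without HBIG. No time to suppression is planned for HBeAg-positive women as a group.

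**Working it through.** **1. The plan's own figure.** The Sample size section gives n = 1.96² × p(1−p)/d². With p = 0.5 and d = 0.08, n = 3.8416 × 0.25/0.0064 = 150.06, which agrees with the stated 150. The target of 170 allows for 1 − 150/170 = 11.8% attrition. No stated figure is in dispute.

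**2. What each analysis uses.**

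| Analysis | Start gestation | HBeAg | What it uses |
|---|---|---|---|
| Kaplan-Meier | only as time zero | no | high/low HBV DNA strata |
| GEE | no | no | baseline HBV DNA, adherence |
| Proportional hazard | only as time zero | no | baseline HBV DNA, adherence |
| Proportion undetectable at delivery | no | no | high/low HBV DNA groups |
| Transmission comparison | yes | no | start time, baseline HBV DNA, adherence |
| Flare models | through treatment duration | no | also HBV DNA at start and delivery |

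**3. Spread in treatment length.** Assuming delivery at 40 weeks (not a figure from the documents), a start at 12 weeks gives 40 − 12 = 28 weeks on TDF by delivery, and a start at 20 weeks gives 40 − 20 = 20. The proportion undetectable at delivery pools women across this range.

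**4. Can the data carry a start-gestation term?**
- The Adherence section expects 10 to 15 women to be detectable at delivery. That leaves between 150 − 15 = 135 and 170 − 10 = 160 suppression events.
- The proportional hazard model would then have three terms, with 135/3 = 45 to 160/3 ≈ 53 events per term.
- Assume start gestation is uniform over 8 weeks: SD = 8/√12 = 2.31 weeks. By Schoenfeld's formula with two-sided 5% and 80% power, the detectable log hazard ratio per week is (1.96 + 0.84)/(√events × 2.31).
- 135 events: 2.80/(11.62 × 2.31) = 0.104, HR 1.11 per week, or 1.52 per 4 weeks.
- 160 events: 2.80/(12.65 × 2.31) = 0.096, HR 1.10 per week, or 1.47 per 4 weeks.
- With only 75 events: HR 1.15 per week, or 1.75 per 4 weeks.

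These figures take start gestation as uncorrelated with the other covariates. Correlation, or starts bunched in part of the window, would raise the detectable effect.

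**5. Size of the HBeAg group.** The Background reports a "hepatitis B e antigen (HBeAg) prevalence of 32.7% in those positive for HBsAg". The share among enrolled women is not given. If it were the same, 0.327 × 150 = 49 to 0.327 × 170 = 56 women would be HBeAg positive. At p = 0.5 the 95% half-width for their proportion undetectable is 1.96 × √(0.25/49) = 14 points to 1.96 × √(0.25/56) = 13 points. That is enough for a descriptive report.

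**The case against.** The strongest reply is that the primary objective needs no start-gestation term. Each woman's clock starts at her own initiation, and the duration needed can be counted back from delivery. This stands. A reader might infer that the trial leaves its start-timing data unused and cannot answer its question, but the documents do not support that: the primary objective is met, and timing also enters the transmission and flare analyses.

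Second, the pharmacokinetic passage contrasts pregnant with non-pregnant patients and states no gradient between 12 and 20 weeks. This also stands. The passage is a reason to check, not evidence that start gestation matters within the window.

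Third, every start falls before 20 weeks, and women who start at the two ends of the window share most of their on-treatment gestation. A start-gestation term therefore says nothing directly about later starts. True; it tests stability within the window only.

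Fourth, HBeAg is not timing data, and baseline HBV DNA, already in both models, may carry much of its information (the documents give no correlation). This is why HBeAg belongs in a descriptive report and not in the argument about timing.

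Fifth, the article is condensed and allows further exploratory analyses. That carries less weight, because the predictors of both models are named and the open clause commits to no particular check.

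**Conclusion.** The point holds in a limited form. The time to suppression is estimated as planned. What is unchecked is the assumption, needed to turn that time into a start in pregnancy, that decline does not depend on gestation at start. The models as named cannot show whether it holds even between 12 and <20 weeks.

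The consequence cannot be put in weeks: the documents give neither a rate of decline for these women nor any effect of start gestation on it. What can be sized is the check. With 135 to 160 events it would detect a hazard ratio of about 1.10 to 1.11 per week, given uniform starts and the article's expectation of 10 to 15 women detectable at delivery. Smaller effects could be missed, so a non-significant term would not prove the assumption.

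This is a moderate, inexpensive improvement to the analysis, not a failure of the primary objective. The HBeAg report is a lesser point.

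**What to change.** - Add gestational age at TDF start, as a continuous covariate, to the proportional hazard model.
- Add it to the GEE together with a start-gestation by time term, so that the rate of decline may differ by start. Report both estimates with 95% confidence intervals, not only a test.
- As a separate descriptive item, report time to HBV DNA below 100 IU/mL and the proportion undetectable at delivery by baseline HBeAg status, beside the high and low HBV DNA groups.
- State that the estimates apply to starts at 12 to <20 weeks, and that any inference to later starts is an extrapolation that the start-gestation term cannot test.

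Both variables are known for every woman at entry, so only analysis wording changes; sample size, visits and sampling stay as they are. The price is one more term in the proportional hazard model, two in the GEE, and slightly wider intervals.

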#### Sample size

We calculated the sample size required to estimate the proportion of pregnant women expected to be undetectable at delivery with precision.

$$n=\frac{{\left(1.96\right)}^{2}p\left(1-p\right)}{d^{2}}$$

There is no prior knowledge to predict the proportion of pregnant women expected to be undetectable at delivery, so we used the most conservative estimate. When this proportion is 50%, the required sample size is the largest. Based on a 95% CI, a margin of error d=8% and a conservative estimation of proportion p=0.5, a sample size of n=150 is required. We aim for n=170 to allow for attrition.

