#### Adherence

The main analysis to determine adherence will be calculating per cent adherence using pill counting data (# pills actually taken/# pills that should have been taken). As a confirmation of adherence, we will also measure TDF concentration in all women with detectable HBV DNA at delivery and in a matched subset of women who become undetectable for comparison (n=2× the number of women who do not become undetectable). This is anticipated to include 10–15 women who are HBV DNA detectable at delivery and matched to 20–30 women who are undetectable. This analytical subsample will be matched on age and initial DNA concentration or, if a matched pair analysis is not feasible because no ‘matching partners’ exist, we will correct for these factors using multivariate regression methods.

The ‘Adherence Starts with Knowledge’ questionnaire ASK-12 is a tool to determine adherence and is derived from the ASK-20 questionnaire.^41^ The questionnaire consists of 12 items related to drug adherence in three scales ‘forgetfulness’, ‘treatment beliefs’ and ‘behavior’. Although previous studies have demonstrated the usefulness of ASK-12 for patients, this tool has not been validated in this study population.^42 43^ Local pilot testing has resulted in a culturally appropriate version of this questionnaire and personnel will be trained to use it. We will use pill counts (gold standard) as well as TDF blood concentration (confirmatory) to validate this tool. The results will be analysed by first comparing differences among the groups, one-way analysis of variance and Bonferroni's multiple comparison tests.

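### The only named missing-data check, complete versus imputed HBV DNA, cannot show whether women lost before delivery were less often suppressed than comparable women who stayed

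*Protocol article*

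**What the plan says.** The HBV viral kinetics section gives the missing-data rule in one sentence: "For missing HBV DNA data, depending on the reasons for being missing, imputations using multiple imputations by chained equations will be used". The check follows: "Sensitivity analyses will then be performed comparing analyses using complete and imputed data sets". After that there is only an open-ended allowance: "Additional analyses may be conducted to further explore the data". The article does not list the imputation predictors, the women whose data inform the imputed values, or the reasons that lead to imputation.

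The proportion undetectable at delivery is a secondary objective, but it is the quantity that sized the study. The Sample size section states: "Based on a 95% CI, a margin of error d=8% and a conservative estimation of proportion p=0.5, a sample size of n=150 is required". It then adds: "We aim for n=170 to allow for attrition". The Adherence section gives the expected number not suppressed: "This is anticipated to include 10–15 women who are HBV DNA detectable at delivery and matched to 20–30 women who are undetectable".

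On follow-up, the Laboratory tests section has HBV DNA measured at every scheduled maternal visit, and the Postpartum follow-up section keeps all women in the study to 4 months after delivery. The Laboratory-based stopping criteria end the drug, not the follow-up.

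**The concern.** A complete-data proportion treats the women without a delivery sample as if they had the same suppression rate as those with one. Chained-equation imputation in its usual form is less strict. It lets the missing women differ in recorded history, such as baseline and earlier HBV DNA, but assumes that women with the same history have the same distribution at delivery whether sampled or not. Neither allows for a woman who does worse after her last visit because she no longer takes the drug.

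The article makes that case foreseeable. The Setting section describes a highly mobile migrant population. It also says that, in August 2017, neither government supplied HBV antivirals in pregnancy and that buying them was unaffordable for this group. A woman who leaves before delivery has therefore probably lost access to TDF. The Background names poor adherence as a main barrier. Table 2 collects pill counts and adherence surveys at visits, so a leaver's record ends while she was still being supplied. Richer predictors cannot recover what happened afterwards.

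The results are meant to inform later studies without immunoglobulin. A delivery proportion that is too high is the unhelpful direction of error, and its interval would not reflect this uncertainty.

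**Working it through.** **1. The plan's own figure.** Inputs from Sample size: z = 1.96, p = 0.5, d = 0.08.

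n = 1.96² × 0.5 × 0.5 / 0.08² = 3.8416 × 0.25 / 0.0064 = 150.06, which agrees with the stated 150. Going from 150 to 170 leaves room for 20 women, or 20/170 = 11.8%. That rate is implied, not stated.

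**2. Assumptions for the illustration.** 170 enrolled, 150 with a delivery HBV DNA and 20 without. All of the 10–15 anticipated detectable women (Adherence section) are among the 150. Let q be the true suppression rate in the 20 missing women. The article gives no value for q, so a range is shown.

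**3. The two stated analyses.**

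- Complete data: (150 − 10)/150 = 93.3%; (150 − 15)/150 = 90.0%.
- Imputation, if the missing women's recorded histories resemble those of the observed: (140 + 20 × 0.933)/170 = 93.3%; (135 + 20 × 0.900)/170 = 90.0%.

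The two coincide whatever q really is, so their comparison shows no difference.

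**4. The true proportion as q varies.** Overall = (observed suppressed + 20q)/170.

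| q | 15 detectable | 10 detectable | Shift from the stated analyses |
|---|---|---|---|
| 75% | 150/170 = 88.2% | 155/170 = 91.2% | 1.8–2.2 points |
| 50% | 145/170 = 85.3% | 150/170 = 88.2% | 4.7–5.1 points |
| 25% | 140/170 = 82.4% | 145/170 = 85.3% | 7.6–8.0 points |
| 0% | 135/170 = 79.4% | 140/170 = 82.4% | 10.6–11.0 points |

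**5. When the shift equals the 8-point margin.** Shift = (20/170) × (observed rate − q). Setting this to 0.08 gives observed rate − q = 0.68. So q = 0.933 − 0.68 = 25%, or q = 0.900 − 0.68 = 22%. The margin is reached only if about a quarter or fewer of the missing women are suppressed.

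**6. Fewer or more missing.** With q = 0 and 170 enrolled, the shift is about 2.7 points for 5 missing, 5.4 for 10 and 16 for 30.

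**The case against.** The strongest reply is that a condensed article need not describe the imputation model, and that a sensitivity analysis for data not missing at random is usual analysis-plan content. As to the model, that stands: the missing predictors and rules are no finding. It does not fully answer the point, because the article does state its check, and that check cannot test the assumption most in doubt. The general allowance for further analyses commits to nothing.

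A second reply is that the two analyses are not the same. If women with high baseline HBV DNA or slow decline leave more often, imputation would move the estimate and the comparison would show it. This is correct. The check is blind only to differences that remain after conditioning on what was recorded.

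Third, Study recruitment and enrolment reports high follow-up in earlier work, tracing after missed visits, and a plan to deliver at the unit as an entry condition. Losses may be fewer than 20, and some samples will be missed for reasons unrelated to the drug. This limits the size, but the study still enrols 20 extra women for attrition.

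A reader might infer more: that women whose TDF is stopped are imputed from women still taking it, and that both analyses must favour suppression. The article does not support this. The imputation model is not described, imputation depends on the reason for missingness, and women who stop TDF stay in follow-up with HBV DNA measured. The direction of bias depends on the missing women being less suppressed than their counterparts.

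**Conclusion.** The point holds for women with no delivery HBV DNA, chiefly those lost before delivery. The one named comparison cannot show whether they fared worse than comparable observed women, and the setting gives reason to think some would. It is a worthwhile improvement to the analysis of a secondary objective that also sized the study. It does not show that the planned estimate is wrong, and the Kaplan-Meier analysis of the primary objective was not assessed here.

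Under the assumptions above, the overstatement is about 2 points if 75% of the missing women are suppressed, about 5 at 50%, about 8 at 25% and about 11 at 0%. A reader might take the 11 points as the expected bias. It is a bound: it needs all 20 places lost, none of those women suppressed, and every anticipated detectable woman among the observed.

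Nor should much be read into whether confidence intervals separate. With 140 suppressed the Wilson intervals are 88.2–96.3% (of 150) and 75.9–87.3% (of 170). With 135 they are 84.2–93.8% and 72.7–84.8%, which overlap. The two sets share the same women, so overlap is not a valid comparison in any case.

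**What to change.** Keep the imputation and the existing comparison. Add one named sensitivity analysis of the proportion below 100 IU/mL at delivery, in which women lost before delivery without a delivery HBV DNA are counted as not below 100 IU/mL. Present this as a bound, with intermediate steps between it and the standard imputation. Two candidates are a return to the woman's own baseline HBV DNA and a delta-adjusted imputation that raises the imputed log10 values by stated amounts. Return to baseline will lie close to the bound, because entry requires HBeAg positivity or HBV DNA above 85 IU/mL. The delta steps therefore give the useful gradation.

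Report beside the results the number of women without a delivery HBV DNA by reason: lost or withdrawn, or sample missed while still in follow-up. Women who stopped TDF and were sampled stay in with their measured values.

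The cost is a few lines of analysis text, one extra table, and a less favourable lower bound. Sample size, visits and treatment do not change.
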